#### Secondary outcomes

The following clinically relevant outcome measures will be compared between the trial arms:
PANSS at 3 monthsPANSS sub-scores at 3 and 6 months (Positive Scale, Negative Scale and General Psychopathology Scale)GAF [39, 40] at 6 months: the assessment is used to rate the social, occupational and psychological functioning of adults. It is divided into two ratings, symptoms and disability, with a score for each. Reliability as measured by intra-class coefficients ranges from 0.81 to 0.94 [41–43]CDS [44] at 6 months, which rates symptoms of depression on a nine-point scale (α = 0.79) [45]Cardiovascular risk factors at 6 months: waist circumference, body mass index, and levels of C-reactive protein (CRP), haemoglobin A1c (HbA1c) and total cholesterol

We will examine all these outcomes for (a) all participants and (b) a subgroup of patients with suboptimal vitamin D concentrations at baseline. We will also measure the efficacy of vitamin D supplementation at 6 months as indicated by the 25OHD blood concentration.

Exploratory measurements include inflammatory and immune markers as well as genetic markers, processed in collaboration with the BioResource for Mental and Neurological Health based at the National Institure for Health Research (NIHR) Maudsley Biomedical Research Centre (London, UK). Participants will be asked to give written consent to allow their blood specimens to be stored for future research, which will be subject to new ethics approvals.

Outcomes will be assessed by objective face-to-face interviews, from information in medical notes or by self-report. All participants will complete outcome measures at baseline, 3 and 6 months (Fig. 1).

### Participant timeline

Following consent and confirmation of eligibility, participants will be randomised to their treatment allocation within 14 days of the baseline assessment. They will attend 6 monthly visits to receive the dose of IMP or placebo. Final outcome measures will be assessed at the Month 6 visit. Each patient will receive a telephone call 28 days after their last dose of IMP/placebo as part of the close-out. The end of the trial will be defined as the last patient last close-out (Fig. 2).

**Fig. 2 Fig2:**
[figure not shown]
Participant flowchart.

### Sample size

Based on the number of new cases presenting to FEP services and annual counts of FEP patients recruited into similar studies, we predicted a recruitment and randomization rate of 120 patients per year for a total of 240. For the primary outcome (measured at the 6-month follow-up), we assumed a 20% attrition rate. Thus, the effective sample size is 192 (96 in each trial arm).

In the PUMP Study [46] (*n* = 190), the mean total PANSS score (and standard deviation) for patients with FEP was 58.1 (15.0). For the power analyses, we modelled two plausible scenarios using 80% and 90% power, respectively, with alpha = 0.05 for both scenarios. Based on alpha = 0.05, power = 80%, and samples with between 200 and 180 participants, we will confidently be able to detect group differences in mean total PANSS score of between 6 and 6.3. This equates to a standardised effect of size of approximately 0.4–0.42. Considering 90% power with the same power assumptions, we will be able to detect group differences in mean total PANSS score of between 6.9 and 7.3 (standardised effect size of 0.46–0.49).

As a secondary objective, we also wish to estimate the average treatment effect in those participants with a vitamin D deficiency at baseline. We assumed that 60% of the FEP population will have vitamin D concentrations below 50 nmol/L at baseline [23]. After 20% attrition at 6 months of the 60% who meet the vitamin D threshold, this will result in a projected sample size of 115. Based on alpha = 0.05, power = 80%, and samples with between 120 and 100 participants, we will confidently be able to detect differences in trial arms for mean total PANSS scores between 7.7 and 8.5 (effect size of 0.52–0.57). Considering 90% power with the same power assumptions, we will be able to detect group differences in mean total PANSS score between 8.95 and 9.8 (effect size of 0.60–0.65).

### Recruitment

To be eligible for entry into the trial, individuals who have experienced their first presentation to health services with psychosis within the last 3 years must satisfy all eligibility criteria. Researchers will visit wards and community services to speak with staff and will meet interested patients face to face or contact them by telephone. Once a patient has agreed to meet for a first appointment, a clinician (i.e. a doctor, research nurse or allied health professional) trained in ICH-GCP will be responsible for obtaining written informed consent. Eligibility will be confirmed by an ICH-GCP trained doctor for all trial participants prior to randomisation. Recruitment strategies will involve liaising with consultants throughout the trust to inform them about the study, visiting in-patient wards, attending physical health clinics in community settings and reaching out to care coordinators about their patients.

### Randomisation

An online randomisation service will be provided by King’s Clinical Trials Unit (King’s College London, London, UK). Randomisation will take place after collection of baseline measures. Randomisation will be stratified according to ethnicity (white or other) at a 1:1 ratio with randomly varying block sizes of 2–4. While there are no known predictors of PANSS scores in our target population, the concentration of vitamin D in blood varies by ethnicity [47], and we hypothesize that this concentration mediates any effect of vitamin supplements.

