Vitamin D deficiency is commonly defined in the UK as levels of 25-hydroxyvitamin D (25OHD) less than 25 nmol/L, insufficiency as between 25 and 50 nmol/L and sufficiency as greater than 50 nmol/L [21]. Those with established psychosis in the UK are highly likely to be vitamin D deficient, with only 14% having sufficient vitamin D levels [22]. This is true even in the early stages of psychosis. Crews et al. examined the vitamin D status of 69 people after their first episode of psychosis (FEP) along with 69 controls of similar age, sex and ethnicity [23]. Over a third had a vitamin D deficiency, while an additional 25% had a vitamin D insufficiency. Overall, the people with FEP had a nearly threefold greater risk of vitamin D deficiency than comparators. Higher vitamin D levels at presentation were associated with lower total and negative symptoms of psychosis a year later [24]. The deficiency in vitamin D seems to be unrelated to other vitamins and minerals. A meta-analysis of nutritional deficiencies in FEP produced the strongest evidence for vitamin D deficiency and some evidence for low levels of vitamin C and folate in FEP, but no evidence for deficiencies in vitamins A and E, or in minerals [25].

People with severe mental illnesses, such as schizophrenia and schizoaffective disorder, experience poor physical health and high rates of premature death [26]. They have higher levels of cardiometabolic risk factors, including higher rates of diabetes, hypertension and central obesity [27–29]. Low vitamin D levels have been associated with cardiometabolic risk in both the general population [30, 31] and in people with established psychosis [22]. Large population-based placebo-controlled studies are currently underway that will examine the influence of vitamin D supplement on general health including cardiometabolic outcomes [32].

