#### Inclusion criteria

Aged between 18 and 65 years old, including women of child-bearing ageHaving a diagnosis of functional psychosis defined according to ICD-10 criteria for psychosis (codes F20–29 and F30–33)Willing to refrain from taking multivitamin or non-study vitamin D supplements that exceed 400 IU per day throughout the studyWilling to give a blood sample to assess vitamin D levels at baselineAble to and have given written informed consent

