### Statistical analysis

Full details of the statistical analyses will be specified in a statistical analysis plan written in collaboration with the trial statisticians.

Descriptive analyses, recruitment rate, consent rate, loss to follow-up, departures from randomised treatment and the prevalence of serious adverse events post-randomisation will be reported and summarised by treatment arm over the course of the study. All causes of withdrawal from the randomised treatment will be reported.

Analyses will be carried out by the trial statistician, who will remain blinded until all analyses are completed. The analysis of vitamin D concentrations in blood samples taken at 6 months, which is a secondary outcome, will be carried out after all other analyses are completed, as there is a high expectation that the mean concentration will be higher in the intervention group.

An intention-to-treat analysis of the effect of vitamin D supplementation on the primary PANSS outcome will be conducted using linear mixed modelling. All the available follow-up data from the randomised participants will be modelled. The analysis model will include treatment arm (vitamin D or placebo), time (3 or 6 months), baseline PANSS and randomisation stratifier (ethnicity) as explanatory variables. The model will also contain a subject-varying random intercept to account for any correlation between the repeated measures. Treatment effects on the other secondary outcomes at 6 months will be assessed using similar modelling techniques, employing generalisations to non-normal data where necessary.

To address the secondary research objectives, we will also estimate treatment effects for the subpopulation who were vitamin D insufficient at baseline in terms of primary and secondary outcomes, except for 25OHD blood concentrations, by including relevant interaction terms between baseline vitamin D insufficiency status and treatment group in the statistical models.

We expect that some data will be missing in the post-treatment outcome variables. The linear mixed modelling analyses are based on maximum likelihood and will provide valid inferences under a missing-at-random missingness mechanism. We will explore predictors of missingness. If deemed suitable for adjustment, we will include these as explanatory variables in the analyses. If post-randomisation variables are identified, a multiple imputation model will be considered instead [49].

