## Discussion

There is a growing body of evidence that suggests vitamin D is neuroprotective [1, 2, 10] and that vitamin D deficiency is prevalent in those with schizophrenia [12, 16]. Longitudinally, the severity of symptoms in psychosis has also been associated with vitamin D concentration [24]. Lack of vitamin D is also associated with physical health problems, including adverse cardiovascular outcomes [50], and so may potentially compound the poor health status associated with psychotic disorders [51, 52]. Few studies have, however, examined whether vitamin D supplementation may improve outcomes among people with psychosis. Our study is the first rigorously designed trial to investigate the impact of vitamin D supplementation in early psychosis.

Our eligibility criteria include only patients who have the capacity to consent to the trial and thus, who have stable and minimal symptoms. We hypothesise that this will minimise the acute effect of the standard treatment on our outcome measures. We have elected not to restrict eligibility to people known to be vitamin D deficient, as it is not standard practice to test vitamin D levels on first presentation with psychosis. Introducing testing prior to study entry would alter clinical practice and introduce a novel clinical question on how to respond to the findings in the absence of applicable evidence. It would also limit the capacity of the study to determine whether there is benefit in supplementing all people with FEP with vitamin D. As we will be analysing baseline vitamin D levels after trial completion, we will be able to conduct a sub-analysis of this patient group.

A key strength of our study is its methodological rigour, since utilising a double-blind randomised controlled trial design removes potential biases inherent in cross-sectional research. The study is designed to take a practical approach and recruit from local clinics. This approach not only enhances the ecological validity of the outcomes but also augments existing connections between clinical and academic networks.

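### The statement that PANSS has no known predictors conflicts with the protocol's own Background, and the primary model omits the baseline 25OHD the trial collects, at a possible small cost in precision

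*Protocol article*

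**What the plan says.** Five places in the protocol article bear on this.

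- **Randomisation.** Allocation is stratified by ethnicity only (white or other). The section says that "there are no known predictors of PANSS scores in our target population", and gives as the reason for choosing ethnicity that "the concentration of vitamin D in blood varies by ethnicity [47], and we hypothesize that this concentration mediates any effect of vitamin supplements".
- **Background.** After describing a study of vitamin D status in first-episode psychosis, it states: "Higher vitamin D levels at presentation were associated with lower total and negative symptoms of psychosis a year later".
- **Discussion.** The same source is used again as rationale: "Longitudinally, the severity of symptoms in psychosis has also been associated with vitamin D concentration".
- **Inclusion criteria.** Participants must be willing to "give a blood sample to assess vitamin D levels" at baseline.
- **Statistical analysis.** The primary linear mixed model has treatment arm, "time (3 or 6 months), baseline PANSS and randomisation stratifier (ethnicity) as explanatory variables", and a random intercept per subject. Baseline vitamin D appears only as insufficiency status, in interactions with treatment for the secondary subgroup objective. The only further covariates foreseen are predictors of missingness.

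**The concern.** The sentence in the Randomisation section is a factual claim about prognosis in the trial's own population, and two other parts of the article do not fit it. The Background presents vitamin D level at presentation as associated with later symptom severity, and the analysis model treats baseline PANSS as worth adjusting for.

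The sentence sits next to a stated covariate list. Baseline 25OHD is the variable closest to the trial's hypothesis, it is measured before treatment, and the subgroup models already need it. It is still absent from the primary model. If it carries prognostic information beyond baseline PANSS and ethnicity, that share of the outcome variance stays in the standard error. Stratifying by two ethnic categories also does not guarantee balance of 25OHD within each category. A visible chance imbalance in baseline vitamin D would invite a post hoc adjustment, which is less convincing than a prespecified one.

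**Working it through.** **1. Set the passages side by side.** Randomisation: no known predictors of PANSS in the target population. Background: in first-episode psychosis, higher vitamin D at presentation went with lower total and negative symptoms at one year. Statistical analysis: baseline PANSS is a covariate. The first statement cannot be kept as worded beside the other two. The Background does not name PANSS, gives no effect size, and does not say whether the association holds after adjustment for baseline symptoms.

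**2. Reproduce the plan's own figures.** Inputs from the Sample size section: SD 15.0, alpha 0.05 (two-sided assumed, since it reproduces the figures), 80% power, 240 randomised, 20% attrition.

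- Effective N = 240 × 0.8 = 192, or 96 per arm, as stated.
- Detectable difference = (1.960 + 0.842) × 15 × √(2/n per arm).
- N = 200: 2.802 × 15 × √(2/100) = 5.94 (5.97 with the t distribution); stated 6.
- N = 180: 2.802 × 15 × √(2/90) = 6.26 (6.30 with t); stated 6.3.
- N = 192: 2.802 × 15 × √(2/96) = 6.07.

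The figures reproduce. They use no covariate, so whether 25OHD is in the model changes none of them.

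**3. What adding baseline 25OHD could gain.** Let r be the partial correlation of baseline 25OHD with 6-month PANSS, given the other covariates. The document gives no value, so r is an assumption. The standard error is multiplied by √(1 − r²), and the equivalent sample size is 192/(1 − r²).

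| Assumed r | SE factor | Fall in SE | Equivalent N | Detectable difference at 80% power, SD 15 |
|---|---|---|---|---|
| 0 | 1.000 | 0% | 192 | 6.07 |
| 0.1 | 0.995 | 0.5% | 194 | 6.04 |
| 0.2 | 0.980 | 2.0% | 200 | 5.94 |
| 0.3 | 0.954 | 4.6% | 211 | 5.79 |

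The last column applies the factor to the unadjusted SD of 15, so it is only a scale. Baseline PANSS will already have reduced the residual SD. If its correlation with the 6-month score were 0.5 (also an assumption), the four differences would be 5.25, 5.23, 5.15 and 5.01. The percentage falls and equivalent N are the same in either case.

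**4. Chance imbalance.** Under simple randomisation with 96 per arm, the standardised difference in baseline 25OHD has standard error √(2/96) = 0.144. An imbalance of 0.2 SD or more in either direction (0.2/0.144 = 1.39 standard errors) would occur in about one trial in six, somewhat less often with stratification by ethnicity. Using SD 15 as an upper scale, its effect on the PANSS difference would be r × 0.2 × 15, or 0.3 to 0.9 points for r of 0.1 to 0.3. The standard error without covariates is 15 × √(2/96) = 2.17 points.

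**5. Feasibility.** Baseline 25OHD precedes randomisation, so it cannot reveal allocation and cannot lie on the pathway from treatment to outcome. The Discussion says baseline levels are analysed after trial completion. That rules out 25OHD as a stratifier but not as a covariate in the final analysis.

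**The case against.** The strongest case on the other side is that only a wording slip remains. Several parts of it stand.

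- A reader might infer that ethnicity is adjusted for as a stand-in for 25OHD. The document does not say so. Ethnicity is in the model as the randomisation stratifier, which is right whatever its prognostic value. The link to 25OHD is the reason for stratifying, and nothing was swapped.
- A reader might infer that the omission biases the primary result. It does not: in a randomised comparison of means, chance imbalance in a baseline covariate is already allowed for in the standard error.
- A reader might take the Background as showing that 25OHD predicts PANSS at 6 months. It reports one observational association, with symptoms at one year, and does not say whether it persists given baseline severity. The gain may be negligible.
- The sentence led to no wrong choice of stratifier, because 25OHD results were not to be available at randomisation.
- Full analysis details are deferred to a statistical analysis plan that is not shown. The subgroup models would also account for vitamin D status if, as is usual, they include its main effect.
- Adjustment is not wholly free: a functional form and a rule for missing assays must be chosen.

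These points limit the size of the finding but do not remove it. The article states its primary covariates and the only kind of addition it foresees. The subgroup models use a dichotomised status for a different objective. The sentence on predictors remains at odds with the Background.

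**Conclusion.** The point stands as a minor, low-cost improvement. The statement on predictors conflicts with the Background and Discussion and with the model's own use of baseline PANSS. The primary model leaves out a collected pre-treatment variable that the protocol's own rationale links to later symptoms.

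Neither the validity of the primary comparison nor the sample size calculation is in question. What may be lost is precision, between almost nothing and about 4.6% of the standard error. That range rests entirely on an assumed partial correlation of 0 to 0.3, for which the document offers no figure.

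**What to change.** 1. In the Randomisation section, correct the sentence on predictors so that it agrees with the Background. The rationale for stratifying by ethnicity can stand without it.
2. Before unblinding, prespecify continuous baseline 25OHD as an additional covariate in the primary PANSS mixed model, beside baseline PANSS and ethnicity. State a simple rule for missing baseline assays, for example mean imputation.
3. Keep ethnicity as the stratifier and in the model. Keep the rule that 6-month 25OHD is analysed after everything else; baseline values do not threaten the blind.

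The cost is one degree of freedom and a line in the analysis specification. Baseline assays must be available before the primary analysis, which the planned subgroup models already require.

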### Intervention

All eligible patients will be randomised to receive once per month either 120,000 IU of vitamin D_3_ (cholecalciferol) (equivalent to 4000 IU per day) or placebo for a maximum of 6 months in a 1:1 ratio. We selected monthly dosing to help with adherence because this clinical group may already have a high tablet burden and are routinely assessed at intervals.

Vitamin D will be given as the drug Vigantol®, which contains vitamin D_3_ (cholecalciferol) in oil. The placebo will be an organoleptically matched triglyceride oil (Miglyol® 812 oil). Both the active medication and the placebo will be packaged in identical sealed glass bottles (fill volume of 8 mL). They will be administered orally as a 6 mL dose given in a graduated oral syringe by a trained researcher. Participants will receive a dose of either active medication or placebo at each monthtly visit over 6 months for a total of six doses. 

Guy’s and St Thomas’ Pharmacy Manufacturing Unit (London, UK) is responsible for arranging the manufacture of the investigational medicinal product (IMP), randomised labelling, packaging and final release by a qualified person for clinical trial use.

No restrictions are placed on prior or concomitant interventions (medications or therapies, rescue or subsequent treatments), other than that we ask the participants to refrain from taking vitamin D supplements (including multivitamins that contain vitamin D) that exceed 400 IU/day for the duration of the trial. This will be checked at baseline and each monthly visit.

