### Safety monitoring

An adverse event is defined as any untoward medical occurrence in a subject to whom a medicinal product has been administered, including occurrences that are not necessarily caused by or related to that product. Any adverse event that occurs between the time of consent to the study through to 28 days following the last dosing visit will be recorded. The principal investigators and study doctors will assess whether the adverse event may be related to the study intervention.

Serious adverse events, serious adverse reactions and unexpected serious adverse reactions are defined as any adverse event, adverse reaction or unexpected adverse reaction, respectively, that results in death, is life-threatening, requires hospitalisation or prolongation of existing hospitalisation, results in persistent or significant disability or incapacity, or results in a congenital anomaly or birth defect. All serious adverse events will be reported for this trial except hospitalisations due to a deterioration in mental state, as we anticipate a high proportion of our participants will be hospitalised for this reason during the trial. All hospitalisations or contact with home treatment teams will be recorded, for example on a service contact form.

In addition, the following assessments will be used to determine subject safety during the study at 3 and 6 months:

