Corrected serum calcium levels (Ca^2+^) will be tested at baseline, at 3 and 6 months, and more frequently if nausea or vomiting occur.At 3 and 6 months, a parathyroid hormone test will be performed on the blood sample if the corrected Ca ^2+^ level is above the normal range. If participants report nausea or vomiting between visits, they will be advised to contact their doctor for a Ca^2+^ blood test.At baseline, female participants will undergo a urine dipstick pregnancy test (testing for beta human chorionic gonadotropin). Female participants of child-bearing age who refuse to take a pregnancy test at baseline will be excluded from participating in the trial. At each treatment visit (monthly for 6 months), the test will be performed again to determine pregnancy status. Pregnancy tests will not be undertaken by female participants who are permanently sterile or who are post-menopausal (no menses for 12 months without an alternative medical cause). If the urine test is positive, the participant will be withdrawn from the trial medication but encouraged to remain in the study. In the event that it is not possible to obtain a urine sample, a blood sample will be obtained and tested for beta human chorionic gonadotropin. No dose of IMP will be administered to female participants without first checking their pregnancy status (except for patients who are permanently sterile or post-menopausal, as described above).

Discontinuation of treatment will occur if a participant begins taking vitamin D doses above 400 IU per day, if they become pregnant, if their parathyroid hormone test is abnormal or at the discretion of the principal investigator.

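### The no-restrictions rule on other medication is inaccurate for prior drugs and lets drugs barred at entry be started during dosing with no stated check or review

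*Protocol article*

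**What the plan says.** The Exclusion criteria section rules out anyone who, in the month before entry, took a drug from six groups: systemic corticosteroids (oral, intramuscular or intravenous), cardiac glycosides, calcium channel blockers, bendroflumethiazide, isoniazid or rifampicin. The Recruitment section has a trained doctor confirm eligibility before randomisation.

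The Intervention section then states the rule on other treatment: "No restrictions are placed on prior or concomitant interventions (medications or therapies, rescue or subsequent treatments". The single exception is non-study vitamin D above 400 IU a day. Of that limit it says "This will be checked at baseline and each monthly visit".

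The Safety monitoring section gives the follow-up checks and stopping reasons. Corrected serum calcium "will be tested at baseline, at 3 and 6 months, and more frequently if nausea or vomiting occur". On pregnancy: "At each treatment visit (monthly for 6 months), the test will be performed again to determine pregnancy status". On stopping: "Discontinuation of treatment will occur if a participant begins taking vitamin D doses above 400 IU per day", on pregnancy, or "if their parathyroid hormone test is abnormal or at the discretion of the principal investigator". Adverse events are collected throughout ("Any adverse event that occurs between the time of consent to the study through to 28 days following the last dosing visit will be recorded") and reviewed for cause: "The principal investigators and study doctors will assess whether the adverse event may be related to the study intervention".

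**The concern.** Two things look wrong. First, a past-month exclusion is a restriction on prior medication, so a sentence saying there is none does not match the eligibility list.

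Second, the drugs were thought unsuitable for someone about to start monthly doses of 120,000 IU, yet the rule for the dosing period leaves them unrestricted. A participant could be prescribed one the day after randomisation. At the next visit the person giving the dose has a stated duty to ask about vitamin D supplements, but none to ask about these drugs, and no study doctor is told to review the case. At stake is a safety precaution that the trial applies at the door and then does not visibly carry through the six doses. The combination with high-dose vitamin D would arise only in the active arm.

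**Working it through.** No arithmetic decides this point. The check is to take four entry conditions and see what the article states for each once dosing has begun.

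| Entry condition | Stated check during dosing | Stated action |
|---|---|---|
| Non-study vitamin D above 400 IU a day | Every monthly visit (Intervention) | Named stopping reason (Safety monitoring) |
| Pregnancy | Every treatment visit, unless permanently sterile or post-menopausal (Safety monitoring) | Named stopping reason |
| Corrected calcium above 2.6 mmol/L | Months 3 and 6, or sooner with nausea or vomiting | Parathyroid hormone test if calcium is above the normal range; an abnormal result is a named stopping reason |
| Any of the six drug groups in the past month | None; falls under the no-restrictions sentence | None named; principal investigator discretion only |

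**Prior medication.** The exclusion criteria restrict it and the Intervention section says nothing does, apart from the vitamin D limit. Taken literally, both cannot be right. Eligibility is confirmed against the full list before randomisation, so the loose word admits no one who should be kept out.

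**Medication during dosing.** An entry exclusion and an on-study rule cover different periods, so there is no contradiction here. The rule is a closed one, however: nothing is restricted except one item, and the monthly check refers to that item.

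**Whether other safeguards close the gap.** Each was tested against one question: would starting one of these drugs set it off?

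- Calcium tests at 3 and 6 months, or on nausea or vomiting: no. They measure calcium and do not detect drug use.
- Adverse-event review: not directly. It may pick up the illness that led to the prescription, but it responds to an event.
- Principal investigator discretion: it can be used for any reason, but only once the investigator knows of the drug.
- The emergency card (Emergency unblinding section): it gives an outside prescriber a route to the trial, if the prescriber sees it and uses it.
- The data monitoring committee (Oversight committees section): it reviews safety periodically, not before an individual's next dose.

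The cover is therefore real but partial, and none of it is triggered by the drug start.

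**Cost of an added question.** The planned sample is 240 (Sample size section) and there are six dosing visits (Participant timeline and Intervention sections), so at most 240 x 6 = 1,440 questions.

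**The case against.** The strongest reply is that this is a condensed journal article. Recording of concomitant medication, pre-dose checks and the rationale for an exclusion list commonly sit in the full protocol, version 10.1, which is not shown. Different rules for entry and for later treatment are normal, and forbidding clinically needed drugs would be hard to defend. The Intervention section also opens by speaking of eligible patients, so a sympathetic reader would already take the sentence as subject to the eligibility criteria. Nor is every other entry exclusion re-screened: the listed illnesses are not.

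Much of this stands, and it rules out several stronger readings that a reader might infer:

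- *That the article expressly permits these drugs.* It does not name them. They are covered only by a general sentence.
- *That giving no reason for the list is itself a defect.* An article may leave the reason to the full protocol.
- *That new medication goes unrecorded.* A sentence about what is forbidden says nothing about what is recorded.
- *That the danger can be sized by counting doses until the next calcium test.* The test does not detect a drug start, so such a count does not measure this gap.
- *That a specific interaction or harm is shown.* The article does not say why each group is excluded.

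The reply does not remove the sentence itself. It is a stated rule with one stated exception and a check tied to that exception, so it is more than something left out for brevity. The comparison with the unlisted illnesses is also imperfect: a new illness would be an adverse event under the article's definition, whereas a new prescription is not one in itself.

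**Conclusion.** The point holds as a minor safety and wording matter. The word for prior medication is inaccurate but has no effect on who enters. For the dosing period, the article states a rule under which a drug that bars entry can be started and dosing can continue with no stated check or review, while other entry conditions are followed up.

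The number of participants affected and the size of any harm cannot be derived from the article. The primary PANSS analysis and the sample size do not depend on the point. The conclusion assumes that the article reports the operating rule faithfully. If the full protocol already has a pre-dose question on these drugs with medical review, only the wording correction remains.

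Timing limits the practical gain. The Trial status section reports that recruitment closed on 14 June 2019 and that follow-up runs to December 2019, so the added check can help only participants still being dosed. The wording can be corrected regardless.

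**What to change.** In the Intervention section, open the sentence with *Beyond the eligibility criteria*, so that it no longer denies the past-month exclusion. Extend the supplement check already made at each monthly visit to ask, before the dose, whether any of the six drug groups has been started.

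In the Safety monitoring section, state that starting one leads to study-doctor review before the next dose, with three possible outcomes: hold, stop, or continue with an extra calcium test. Say plainly that participants are not asked to decline treatment their clinicians prescribe. If the list is meant to apply at entry only, a sentence saying so would settle the dosing-period question.

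The cost is wording in two sections, one question at visits that already take place (the 1,440 maximum above), and possibly an occasional dose delayed until a doctor has looked at the case. No extra staff or visits are needed.
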